## Abstract

**Background:**

Comparative effectiveness research (CER) documents important differences in antidepressants in terms of efficacy, safety, cost, and burden to the patient. Decision aids can adapt this evidence to help patients participate in making informed choices. In turn, antidepressant therapy will more likely reflect patients’ values and context, leading to improved adherence and mood outcomes.

**Methods/Design:**

The objective of this study is to develop the Depression Medication Choice decision aid for use during primary care encounters, and to test its efficacy by conducting a clustered practical randomized trial comparing the decision aid to usual depression care in primary care practices.

We will use a novel practice-based, patient-centered approach based on participatory action research that involves a multidisciplinary team of designers, investigators, clinicians, patient representatives, and other stakeholders for the development of the decision aid. We will then conduct a clustered practical randomized trial enrolling clinicians and their patients (n = 300) with moderate to severe depression from rural, suburban and inner city primary care practices (n = 10). The intervention will consist of the use of the depression medication choice decision aid during the clinical encounter. This trial will generate preliminary evidence of the relative impact of the decision aid on patient involvement in decision making, decision making quality, patient knowledge, and 6-month measures of medication adherence and mental health compared to usual depression care.

**Discussion:**

Upon completion of the proposed research, we will have developed and evaluated the efficacy of the decision aid depression medication choice as a novel translational tool for CER in depression treatment, engaged patients with depression in their care, and refined the process by which we conduct practice-based trials with limited research footprint.

**Trial registration:**

Clinical Trials.gov: NCT01502891

## Background

Depression is one of the most common chronic illnesses in the USA, and decreases the quality and duration of life of over 16 million Americans. Impacting not only individuals, depression causes suffering to family and friends, losses in productivity, and other costs to society [1]. Despite a lifetime prevalence of 17%, depression is often undetected and suboptimally managed, particularly in primary care where 80% of patients with depression receive care and 75% of antidepressant prescriptions are provided [2,3]. Unfortunately, adherence to antidepressants is low, with contemporary cohorts citing 6-month rates in the range of 13% to 60% [4,5], and many patients who are initially adherent discontinue prematurely [6]. Primary nonadherence and premature discontinuation are associated with 77% increased risk of relapse or recurrence, and adverse effects on disability and healthcare utilization [7-9]. Thus, even when patients with depression are detected and diagnosed properly, over 60% will have adequate fidelity to treatment and many will suffer protracted clinical course with great cost implications in terms of dollars and human suffering.

Lifestyle changes, self-care practices, evidence-based psychotherapy and pharmacotherapy can improve depression outcomes, lower healthcare costs and improve the quality of life. When it comes to pharmacotherapy, depression care often demands primary care clinicians’ and patients’ use of therapy and medication regimens of different efficacy, safety, cost, and burden to the patient; findings vary according to depression severity and recurrence, underscored by the emerging literature on their comparative effectiveness [10,11]. Moreover, the translation of the evidence from comparative effectiveness research (CER) remains limited [12].

Patient decision aids can facilitate the translation of CER into practice. When systematically summarized, CER can inform the content of decision aids, including the range and likelihood of desirable and undesirable outcomes across the different options. These tools can be designed to facilitate patient involvement in making decisions even among patients and clinicians with limited experience in shared decision making [13-15]. We have previously shown that decision aids that provide easily accessible information about treatment options and their outcomes for other chronic conditions facilitated knowledge transfer and greater patient involvement in usual primary care settings, and showed promise in improving adherence to therapy [14,16,17]. To our knowledge, there is no research evaluating the use of patient decision aids within the clinical encounter, to facilitate the participation of patients with moderate to severe depression in choosing antidepressants in practice.

Consequently, to determine the ability of a decision aid to effectively translate CER about antidepressants into practice, we will first develop a decision aid, the Depression Medication Choice, for use during primary care encounters that would meet the needs of key stakeholders (patients and clinicians, health plans, and payers), while enabling shared decision making as a way of translating antidepressant CER into practice. We will then enroll primary care practices and randomly assign these to either usual depression care or to care involving use of the depression medication choice decision aid*.* This trial, still underway, will generate preliminary evidence of the relative impact of the decision aid on patient involvement in decision making, decision making quality, patient knowledge, and 6-month measures of medication adherence and mental health compared to usual depression care.

## Methods/Design

### Development of the Depression Medication Choice decision aid

We will use a novel practice-based, patient-centered approach for decision aid development based on design/participatory action research, developed and validated by the Knowledge and Evaluation Research Unit at Mayo Clinic (Rochester, MN, USA), and executed by a multidisciplinary team comprised of designers, patients, primary care and psychiatry clinicians, and decision making and health literacy scientists (Figure 1) [13,14,17].

**Figure 1 F1:**
[figure not shown]
Development of a decision aid.

This approach includes three main steps: 1. synthesis of clinical evidence regarding the risks and benefits of each option, and its approval by stakeholders; 2. observations of real-time clinical encounters involving clinicians and their patients with depression facing the decision to use antidepressants; and 3. prototyping of the decision aid through a series of iterations and field testing in the same context as the initial observations.

#### Synthesis of evidence

For the purpose of the development of the depression medication choice decision aid, we will synthesize the evidence regarding the risks and benefits of antidepressants based on the Agency for Healthcare Research and Quality (AHRQ) effective healthcare systematic review report on the comparative effectiveness of second generation antidepressants (07-EHC-007) [18]. We will then convene psychiatrists, primary care clinicians, patients and health plan representatives to meetings in which they will review the summary, and agree on its results and associated credibility and applicability.

#### Observation of encounters

Members of the research team led by a designer will observe approximately 10 to 15 usual clinical encounters, typically 3 to 5 without aids, and 3 to 5 with each iteration of the decision aid prototype. Using a predefined observation grid we developed and used in previous studies, we will look for patterns of patient-clinician conversations regarding antidepressant medications, as well as nonverbal behaviors and attitudes.

#### Prototyping and field testing

The construction of the Depression Medication Choice will be based on the summary of evidence and clinical observations, guided by the International Patient Decision Aid Standards (IPDAS) [19], which provides recommendations and standards for the development of decision aids. The initial prototype of the decision aid will result from discussions with members of the study team, clinicians, and patients from our patient advisory groups. They will be asked to comment on the content, format and ease of use of the prototype, on how the prototype aid captures current knowledge and addresses their concerns about antidepressants, and on to what extent the prototype helps bring to light patient context, values and preferences for decision making. Once developed, we will pilot this initial prototype in 3 to 5 clinical encounters, looking for patterns of the conversations, and documenting the issues, problems and challenges. When feasible, we will conduct a brief structured interview with the patient and the clinician after the encounter. The study team will then evaluate the quality of the conversations and the ability of the prototype to facilitate the decision making process. This process will be repeated with subsequent prototypes until the research team and stakeholders reach a consensus that the prototype is successful in involving patients in decision making (in our prior work it has taken up to seven iterations). This process should result in a discrete and highly intuitive decision aid, requiring minimal training to use, and designed to meet the needs of patients and their primary care clinicians working in fast-paced care settings.

### Evaluation of the impact of the Depression Medication Choice decision aid

#### Study design and setting

We will conduct a clustered, practice-based, randomized trial of the Depression Medication Choice decision aid in ten rural, suburban and inner city primary care practices in the Midwest USA. The Mayo Clinic Institutional Review Board (IRB) has approved the study procedures described herein. We also obtained ethical approval from Hennepin County Medical Center Human Subjects Research Committee for the three participating practices not covered under the Mayo Clinic IRB. The trial design and protocol are registered in ClinicalTrials.gov (http://NCT01502891).

#### Study participants

Primary care practices were invited to participate in the study based on key criteria for a successful collaboration identified from past similar trials: sufficient number of clinicians interested in participating; an easily identifiable clinical champion; a large enough patient population meeting our inclusion criteria; and an on-site, or willingness to have an on-site, study coordinator. Practices that had concurrent research studies involving antidepressants were automatically excluded from participating in the study.

Primary care clinicians (physicians, nurse practitioners, physician assistants) from participating practices will be eligible for the study if they provide care to patients suffering from depression. Eligible clinicians will be invited to participate in the study through an initial meeting held by the investigators at the practice or individually by the on-site study coordinator.

Adult patients will be eligible for the study if they have a diagnosis of depression as judged by the clinician, a score on the Patient Health Questionnaire (PHQ-9) ≥10 [20], receive their depression care in the primary care setting, do not have bipolar disorder (as judged by the clinician), and have no major barrier (language, sensorial, cognitive) to providing written informed consent.

Eligible patients will be identified in advance from the appointment schedules of clinicians. All eligible patients who present to the practice for a depression visit during the study will be invited by an on-site study coordinator to participate in the study.

#### Allocation procedures

We will randomly allocate practices to the intervention or usual care arm. We will pair practices by size (the number of clinicians seeing adult patients with depression) and by whether they have implemented the DIAMOND (Depression Improvement Across Minnesota, Offering a New Direction) program, a practice redesign initiative to improve depression care through the use of care coordinators [21]. Within each pair, we will randomize practices to either: 1. the use of Depression Medication Choice within the clinical encounter; or 2. usual care. A study statistician will perform the randomization centrally after the practices have been enrolled and ensure concealment of allocation.

Practices, clinicians and investigators will not be masked to allocation. However, patients will remain unaware of the study’s main hypotheses. To prevent loss to follow-up and support the intention-to-treat principle, we will centrally follow patients, and ensure that patient surveys and pharmacy follow-ups are complete.

#### Intervention

The intervention will consist of the use of the Depression Medication Choice decision aid by patients and their primary care clinician during the clinical encounter. Training of clinicians will be provided prior to enrollment of their patients and will include a demonstration showing how to use the decision aid with patients. The focal points of the demonstration will be: 1. the decision aid serves as a guide for conversation rather than a script; 2. clinicians have flexibility in the manner in which they use the decision aid, including how and when they use it during the visit; and 3. clinicians may elect not to use the tool with certain enrolled patients, per their own judgment. Brief video clips and a storyboard to demonstrate the basic use of the decision aid will be available for clinicians to review at their convenience. A study team member will remain available to undertake one-to-one demonstrations after the initial group demonstration, as needed.

#### Usual care

For patients in the usual care arm, clinicians will manage the discussion about medication regimen as usual, without using the decision aid.

#### Data collection and analysis

We will collect patients’ data through: 1. self-reported questionnaires administered before and after the clinical encounter with their clinician, and at 3 and 6 months post-encounter; and pharmacy data 2. information about depression-related care included in medical records. Participating clinicians will be given brief questionnaires to complete once before and then immediately following each clinical encounter with a participating patient. In addition, we will videotape each clinical encounter where consent to do so has been provided by both the patient and clinician. Patient, clinician and practice socio-demographic information will be collected through questionnaires, and administrative or patient medical records.

#### Outcomes measures

The RE-AIM framework, developed to address how an intervention is implemented in a real-world setting, will guide this portion of the study and includes the following dimensions: Reach (how broadly is this intervention used within the practices), Effectiveness (what is the impact of the intervention on outcomes), Adoption (can this be adopted by new groups with ease and minimal modifications), Implementation (what are the special issues and barriers in implementation), and Maintenance (can the intervention be maintained and will the impact continue) [22,23].

To assess the Reach of the decision aids, we will use a tracking log to record patients who are enrolled as well as those who declined the invitation to participate, and their respective characteristics. This will allow us to measure participation and representativeness.

To assess the Effectiveness of the decision aids, we will measure patient decisional conflict as the primary outcome, and decision making quality and processes (that is knowledge, satisfaction, preference in decision making style, patient involvement in decision making), depression outcomes, and medication adherence as secondary outcomes in the following ways:

1 Decisional conflict*.* Patients will complete the decisional conflict scale (DCS) immediately after the clinical encounter, the most commonly used outcome measure in decision aid trials [24,25]. Psychometric properties include good internal consistency, test-retest reliability, and effect sizes for responsiveness to change ranging from 0.4 to 1.2. Clinicians will also complete a similar scale immediately after the clinical encounter [26].

2 Knowledge*.* Patients will complete a questionnaire addressing general and specific knowledge about depression care contained in the decision aids. This questionnaire will be developed according to prior recommendations and will be completed after the encounter, and at 3 and 6 months post-encounter.

3 Satisfaction*.* Patients and clinicians will be asked questions regarding the acceptability and satisfaction regarding the way information was shared during the encounter.

4 Preference. Patients will identify their preference in decision making style prior to and after the encounter [27]. Clinicians will also complete the same questionnaire at enrollment in the study and following each encounter with a participating patient.

#### Socio-demographic and other patient characteristics

At entry in the study, patient characteristics collected will include age, gender, marital status, education, income, subjective health literacy [30,31] and subjective numeracy [32]. We will collect the following clinician characteristics: gender, birth year, position, practice specialty and number of years in practice. Practice-level characteristics will include distribution of patient ethnicity, race, payment method, population of community, location of clinic (urban, suburban, rural), distribution of full-time equivalent across staff (clinicians, nursing staff, educators), average number of visits per week and average length of appointments.

#### Sample size

The Statin Choice randomized trial evaluated the decision quality by comparing the decision aid to usual care, and reported a 9.8 point difference in decision quality with the standard deviation (SD) of 16.9 and 14.1 for the usual care and decision aid groups, respectively [16]. Thus, to determine the statistical power of the current trial, we made the following assumptions: 1. variances will be as reported in the statin choice study; 2. the trial should detect a difference of 9.8 points or greater in decisional conflict between two groups at a significance level of 0.05, with a two-sided t-test; 3. a modest correlation of outcomes within practices represented by an intracluster correlation coefficient (ICC) (between cluster variance/total variance) of 0.05; and 4. a 10% attrition rate. We estimated the power using a standard calculation for a t-test, adjusted for clustering by a variance inflation factor (VIF) (1 + (n - 1) x ICC), where n is the number of patients per practice [33]. Under these assumptions, we estimated that we will have 90% power to detect at least a 9.8 difference in the DCS if we are able to recruit 30 patients per clinic for a total recruitment target of 300 patients. Assuming a similar ICC and attrition rate for other outcomes, this sample size will have 99% power to detect 1 SD difference in any continuous measure (for example approximately a 2-point difference in a 10-question knowledge scale), and 80% power to detect a 30% difference in 6-month adherence rates assuming a control adherence rate of 50%. Actual power is likely to be greater because we will adjust for baseline values and characteristics, and because of our conservative assumptions.

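### The 90% power stated for the primary outcome needs a large-sample reference distribution; with ten randomized practices (8 df) the same inputs give about 82–85%

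*Protocol article*

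**What the plan says.** The protocol article's Sample size section sets the target as to "detect a difference of 9.8 points or greater in decisional conflict between two groups at a significance level of 0.05, with a two-sided t-test". It takes a "standard deviation (SD) of 16.9 and 14.1 for the usual care and decision aid groups, respectively" from an earlier decision aid trial, and assumes an "intracluster correlation coefficient (ICC) (between cluster variance/total variance) of 0.05" and "a 10% attrition rate". Power comes from an ordinary t-test calculation with the variance multiplied by 1 + (n − 1) × ICC, where n is the number of patients per practice. The result is "we estimated that we will have 90% power to detect at least a 9.8 difference in the DCS", given 30 patients per clinic and 300 in total. The section closes: "Actual power is likely to be greater because we will adjust for baseline values and characteristics, and because of our conservative assumptions".

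Study design and setting gives ten practices. Allocation procedures makes the practice the unit of randomization, paired on size and on use of a depression care redesign program: "Within each pair, we will randomize practices to either" arm. The Analysis section plans cluster-adjusted t-tests for unadjusted comparisons and hierarchical models for adjusted ones. It does not mention the pairs. Outcomes measures times the primary outcome thus: "Patients will complete the decisional conflict scale (DCS) immediately after the clinical encounter".

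**The concern.** Inflating the variance for clustering makes the standard error right on average. It does not change how well that standard error is estimated. The treatment comparison rests on variation between practices, and there are five practices per arm. An unpaired test therefore refers to a t distribution on 10 − 2 = 8 df, whose two-sided 5% critical value is 2.306, against 1.97 on 268 df. A calculation that inflates the variance but keeps a large-sample critical value overstates power, and with so few clusters the difference is visible.

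At stake is the headline power for the primary outcome. If the true figure is 82–85%, the chance of missing a real 9.8-point effect is 15–18%, not 10%, and a null result would invite a firmer reading than the design supports. If the analysis instead used the large-sample critical value, power would be near the stated figure but the 0.05 level would not hold.

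**Working it through.** **Inputs (Sample size, Study design and setting, Allocation procedures).** Difference 9.8; SDs 16.9 and 14.1; ICC 0.05; two-sided 0.05; five practices per arm; 30 recruited per practice; 10% attrition, so 27 evaluable per practice and 5 × 27 = 135 per arm.

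**Common quantities.**
- Averaged SD = √((16.9² + 14.1²)/2) = √242.21 = 15.56.
- VIF = 1 + (n − 1) × 0.05. The article does not say whether n is before or after attrition: n = 30 gives 2.45, n = 27 gives 2.30.
- Effective n per arm = 135/2.45 = 55.1, or 135/2.30 = 58.7.
- Standard error = 15.56 × √(2/effective n) = 2.965, or 2.873.
- Noncentrality = 9.8/2.965 = 3.31, or 9.8/2.873 = 3.41.
- With no attrition (150 per arm, VIF 2.45): effective n 61.2, standard error 2.813, noncentrality 3.48.

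**Power for 9.8 points, two-sided 0.05.**

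| Reference distribution | 27 evaluable, VIF 2.45 | 27 evaluable, VIF 2.30 | 30 evaluable, VIF 2.45 |
|---|---|---|---|
| Normal | 91.1% | 92.7% | 93.6% |
| t, patient-level df (268; 298 if all 30 evaluable) | 90.9% | 92.5% | 93.5% |
| t, df from effective sample size | 90.6% | 92.3% | 93.3% |
| t, 8 df (ten practices) | 82.4% | 84.7% | 86.1% |
| t, 4 df (five pairs, pairing removes no variance) | 69.9% | 72.4% | 74.1% |

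The first three rows reproduce the stated 90%, most closely with VIF 2.45. No 8-df version with the averaged SD reaches it.

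**Check by simulation.** In 200,000 simulated trials of practice means with the two stated SDs and 27 patients per practice, power was 84.7% on 8 df and 72.7% for the paired test on 4 df. The 268-df critical value gave 91.2% power, but a type I error of 8.5%. Directly, the 268-df critical value of 1.969 referred to t on 8 df has a two-sided tail of 8.4%.

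**Detectable difference at 90% power, 8 df.** The noncentrality needed is 3.712. Multiplied by the standard error: 3.712 × 2.873 = 10.7 and 3.712 × 2.965 = 11.0 points; with no attrition, 3.712 × 2.813 = 10.4.

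**If the pairs were analysed.** The 4-df row depends on how much between-practice variance the pairing removes, which the article does not give. With VIF 2.30 and an assumed share of 0%, 30%, 50% or 70% removed, 4-df power is 72%, 80%, 85% or 91%.

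**Dependence on the ICC.** With 27 evaluable, 8-df power is 92% at an ICC of 0.03 and 67% at 0.10. The 0.05 used above is the article's own value.

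**The case against.** The article names its method, and its figure follows from that method. This is a disclosed approximation without a small-cluster correction, not a slip in arithmetic. That stands. A reader might infer that the authors used patient-level degrees of freedom, but the article gives none. All that can be said is that, on its inputs, only a large-df calculation arrives at 90%.

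A reader might also infer that the design's real power is 70–72%. The article does not support this. It describes no paired analysis, and those figures assume that pairing on size and program status removes no variance between practices. They are conditional on both.

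It is likewise tempting to say that the closing sentence of the section has no basis. That goes too far. It refers to baseline characteristics as well as baseline values. Demographics, health literacy and numeracy are collected at entry, PHQ-9 is measured before the encounter, and adjustment is planned where groups differ. If covariates explained 10–20% of the variance at both levels (an assumption), 8-df power with 27 per practice would be 88–91%. The attrition allowance is also cautious for a questionnaire completed right after the visit. Removing it altogether raises 8-df power to 86%, still short of 90%.

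Finally, the trial is described as giving preliminary evidence, recruitment is under way, and every 8-df figure at the stated ICC and averaged SD exceeds 80%. This limits the consequence but does not make the stated figure correct.

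**Conclusion.** The concern holds for the main comparison. Power of 90% for 9.8 points at a two-sided 0.05 level is not a property of a ten-practice design under the article's own inputs. On 8 df it is about 82–85% with 10% attrition, and 86% with none. Against the large-df figures that reproduce the claim, the loss is about 7–9 percentage points. This is moderate, but it concerns the primary outcome.

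The result assumes equal practice sizes, an ICC of 0.05, the averaged SD and an unpaired analysis without covariate gain. The closing sentence on greater power cannot stand unqualified. No baseline DCS is described, any gain from other characteristics is unquantified, and a calculation that omits the cluster-level degrees of freedom cannot be called conservative on that account.

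**What to change.** In Sample size, state the reference distribution and restate primary power as about 82–85% for a 9.8-point difference (t on 8 df, 10% attrition), with 90% power for about 10.7–11 points. If an analysis respecting the five pairs is made primary, give its figure too: about 70–72% on 4 df if pairing removes no between-practice variance, and higher to the extent that it does, with the assumed share stated.

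Remove the sentence on greater actual power, or qualify it by saying that no baseline DCS is available and that any gain from other baseline characteristics has not been quantified.

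Enrolment should not change. The cost is rewording one paragraph and accepting a less favourable figure; no patients, visits or data are added.
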